## **11. Statistical Analysis**

SAS will be used to perform the statistical analyses. The general approach to analysis is described below. A full SAP, which documents and details all data handling rules and prospective statistical analyses, will be finalized prior to completion of participant enrollment.

Baseline and demographic characteristics will be summarized descriptively. The study's demographic characteristics, baseline values, the primary outcome and secondary outcome will

be summarized descriptively through the tabular display of mean values, medians, ranges, and standard deviations for continuous variables of interest and frequency distributions for categorical variables.

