| Clinical Study Type            | Single arm interventional cohort study                                                                                                                                                                                                                                                                                                                                                                                                                                                                                                                                                                                                                                              |
| Name of Device                 | Better Therapeutics' Nutritional Cognitive Behavioral Therapy (BT-NCBT-00x)                                                                                                                                                                                                                                                                                                                                                                                                                                                                                                                                                                                                         |
| Sponsor                        | Better Therapeutics, Inc
[name]
[name]                                                                                                                                                                                                                                                                                                                                                                                                                                                                                                                                                                                                    |

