|  | 
participants will be screened and consented by the research team, per the procedures listed below. FibroScan will be used to screen individuals likely to meet the PDFF primary endpoint analysis criteria of a liver fat fraction greater than or equal to 10% at baseline. All participants will be included in secondary and exploratory endpoint analysis.
 
Labs and imaging will be collected at screening visit to confirm eligibility requirements and establish a baseline, then again at the end of the intervention to assess therapeutic impact. Participants will also be asked to complete qualitative assessments to evaluate their experience using the study intervention and the impact of treatment on their quality of life.
 
The full Schedule of Assessments is provided in Table 1 within the protocol.
 
The treatment, BT-NCBT-00x, consists of a software as a medical device developed by the study Sponsor, Better Therapeutics. It delivers treatment to participants with cardiometabolic disease, using behavioral therapy that targets individual behaviors related to improving dietary quality and physical activity. BT-NCBT-00x is accessed via the participants' smartphone after downloading from the phone's corresponding app store.
 
Participants will receive behavioral support by the Better Therapeutics patient services team in the form of an orientation and wrap-up call. The intent of the Treatment Orientation Call is to introduce participants to the nature of the treatment and assess readiness to engage in behavioral therapy. In this call, participants will also receive education on evidence-based behavioral strategies for NAFLD treatment that are not yet fully integrated into BT-NCBT-00x, such as the benefit of reducing intake dietary saturated fat and replacing with monounsaturated and polyunsaturated fatty acids. The wrap-up session is intended to allow the Better Therapeutics team to gather feedback about participants' experiences using the intervention. The study population will also be monitored by the Better Therapeutics Population Health Nurse Practitioner and participants will be offered additional behavioral
 |

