## 5.3 Study Enrollment

Participants who are consented and eligible for participation will be referred by the study site to begin treatment with the BT-NCBT-00x study App. Referral requires clinic staff to enter the patient's unique ID, mobile phone number, and email into the Better Therapeutics Study Portal. The portal is secure and HIPAA compliant.

Once referred, the participant will receive an email and text with link directing them to a secure website to create an account for the study intervention (see Appendix 17.1). Account creation will require participants to provide an email address, mobile phone number, first name and last name. This information will be validated against the values added to the Study Portal by the Arizona Liver Health delegated staff to confirm the App is being downloaded by the correct individual. The creation of the account triggers an SMS with a link to download the App from the app store appropriate to the phone type. Enrollment in the study will be completed once a participant completes the self-directed onboarding within the App. Participants who do not complete App-onboarding will be considered screen-failures and replaced.

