Skill exercises are intended to provide an opportunity for participants to practice skills related to behavioral beliefs. The method by which participants must practice these skills is designed to enhance executive function tasks such as planning, problem solving and goal setting. Each lesson explains the rationale and benefits of the skill exercise in reference to the core topic being explored.

In addition to completing a lesson (and one or more skill exercises), BT-NCBT-00x directs patients to self-report diet and exercise behaviors, medication adherence, and biometrics (e.g., weight). If the patient has comorbid Type 2 diabetes or hypertension, he or she will also be able to self-monitor fasting blood glucose and blood pressure each day. Weekly behavioral goals, including diet and exercise behaviors, are determined through a goal setting exercise, and are advanced in a manner most likely to maintain or increase self-efficacy. When self-efficacy is high, the participant has a high probability of achieving his or her goals.

Participants will be directed to engage with one lesson each week of the study, to report plant-based meals consumed and minutes of exercise completed and, if indicated, to measure

their blood glucose and/or blood pressure daily. All participants will be given access to the App for 3-months.

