## 5.5 Product Support

A selection of patient services will be provided over the course of the study. Participants will be expected to complete two calls with a behavioral specialist: the Treatment Orientation Call will be completed prior to the start of intervention and a wrap-up call completed at the end of the intervention. The Treatment Orientation Call is intended to help introduce the participant to the nature of the treatment and assess readiness to engage in behavioral therapy. In this call, participants will also receive education on evidence-based behavioral strategies for NAFLD treatment that are not yet fully integrated into BT-NCBT-00x, such as the benefit of reducing dietary intake of saturated fat and replacing with monounsaturated and polyunsaturated fatty acids. The wrap-up session is intended to allow the Better Therapeutics team to gather feedback about participants' experiences using the intervention.

The study population will also be monitored by a Nurse Practitioner to assess participants' engagement and biometric progress. Users who are not meeting expected thresholds for engagement or biometric progress will be offered additional support in the form of a call with a behavioral specialist or nurse practitioner to help identify barriers to behavioral therapy and develop a plan for addressing these potential obstacles to improve treatment adherence and efficacy. Sample screen images of support messages and call scheduling ability in the App can be seen in Appendix 17.3.

A product support specialist will be available over the length of the study to provide support for participants who need help using BT-NCBT-00x. If a participant's needs are beyond the scope of technical product support, the product support specialist will refer the participant to the clinical care team for behavioral support. In addition, a behavioral support specialist may proactively reach out to patients to offer more support to help them get the most out of using BT-NCBT-00x. Participants will be free to accept or turn down any offer of support.

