## **10. Analysis Populations**

For purposes of analysis, the following populations are defined.

- Enrolled: All participants who complete the onboarding and first time user experience steps within the App for the first treatment cycle assigned. This population will be utilized for all safety summaries;
- Per Protocol: Participants who are enrolled and complete a minimum number of lessons in the App during the intervention period, as pre-specified in the Statistical Analysis Plan (SAP). This population of participants will be the Intent to Treat (ITT) group for analysis;

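### The SAP deadline is the end of enrolment, so pre-specification of the lesson cut-off that defines the 'ITT' group is not guaranteed

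*Protocol*

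**What the plan says.** Section 11 of the Protocol puts all data handling rules and prospective analyses in a SAP that "will be finalized prior to completion of participant enrollment". No other date is attached to the SAP.

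Section 10 defines the Per Protocol set as enrolled participants who "complete a minimum number of lessons in the App during the intervention period, as pre-specified in the Statistical Analysis Plan (SAP". It gives no number and adds: "This population of participants will be the Intent to Treat (ITT) group for analysis".

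The design is given in the Synopsis as "Single arm interventional cohort study". Section 5.3 states: "Enrollment in the study will be completed once a participant completes the self-directed onboarding within the App". A footnote to Table 1 makes that same event treatment Day 1. Section 5.4 sets the lesson pace: "Participants will be directed to engage with one lesson each week of the study". It also has participants report weight and other biometrics in the App.

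On oversight during treatment, Section 5.5 says: "The study population will also be monitored by a Nurse Practitioner to assess participants' engagement and biometric progress". The Synopsis places this nurse practitioner with the sponsor: "The study population will also be monitored by the Better Therapeutics Population Health Nurse Practitioner". Section 12 keeps App data on the sponsor's servers and site data in a separate system. Section 13 restricts App data to authorised personnel in de-identified form. Table 1 and the Synopsis (Total Study Duration) place the outcome MRI between Day 90 and Day 104.

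**The concern.** With about 10 participants expected in the primary analysis, moving the cut-off by a lesson or two can remove a sizeable share of the data. A rule with that much influence should be fixed before anyone can see how it would change the result. The only timing rule in the protocol does not secure this, because it runs to the last participant's enrolment rather than the first.

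If the cut-off were chosen with knowledge of responses, or of a proxy such as weight change, the choice would tend to favour improvement. The t-test p-value could then no longer be read at its nominal level. No control arm is there to absorb the bias.

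Leaving the number itself to the SAP is ordinary practice and is not the complaint. The complaint is the deadline that the protocol sets for the SAP.

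**Working it through.** **1. The plan's own figures.** Section 9 assumes a mean change of -2.4 with SD 1.6, alpha 0.05, about 90% power and 8 evaluable participants. The standardised effect is 2.4/1.6 = 1.5. Exact power of the one-sample t-test (noncentral t, two-sided 0.05) is 90.8% at n=7 and 95.1% at n=8, so 8 is adequate. With 20% attrition, 8/0.80 = 10. The sample size is not in dispute; n=10 is carried forward as the size of the primary analysis.

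**2. App data before the deadline.** Enrolment of a participant is App onboarding, which is Day 1. The last participant's Day 1 closes enrolment, and everyone enrolled earlier already has App data accruing by then. This holds for any accrual length.

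**3. Outcome MRIs before the deadline.** If 20 participants enrol evenly over A days, the number whose MRI can precede the end of enrolment is about 20 × (A − 104)/A to 20 × (A − 90)/A, for MRI at Day 104 or Day 90. A is an assumption because the protocol states no accrual period.

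| Accrual (days) | MRIs possible, of 20 |
|---|---|
| 90 or less | 0 |
| 120 | 20×16/120 = 2.7 to 20×30/120 = 5.0 |
| 180 | 20×76/180 = 8.4 to 20×90/180 = 10.0 |
| 270 | 20×166/270 = 12.3 to 20×180/270 = 13.3 |

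Section 9 expects about half of the 20 to qualify for the primary analysis. Scaled to 10, 120 days gives about 1 to 3 known outcomes and 180 days about 4 to 5.

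**4. Effect on the error rate.** Illustrative simulation, n=10. Assumptions: no true change, lesson counts uniform on 0 to 13 and unrelated to outcome, cut-off picked from 1 to 12 as the most favourable among the outcomes seen, at least 5 participants kept. The rate is that of a significant result in the direction of benefit, nominal 2.5%.

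| Outcomes seen when the cut-off is picked | False-benefit rate |
|---|---|
| Cut-off fixed in advance | 2.2% |
| 2 of 10 | about 2.6 to 2.8% |
| 5 of 10 | about 3.2 to 4.0% |
| 10 of 10 (not reachable under the deadline) | about 5.2 to 5.4% |

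The ranges reflect repeat runs and how the best cut-off is scored; the 2.2% differs from 2.5% by simulation error. The mean shift with half seen is about 0.1 points towards benefit, against a planned change of -2.4.

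**5. App data without MRI.** If lesson counts are unrelated to outcome and only lesson counts are seen, the error rate stays nominal. If the cut-off is picked on App weight change, and weight change is assumed to correlate 0.7 with liver-fat change, the rate with 8 of 10 weights known is about 3.4 to 3.7%. The correlation is an assumption; the protocol gives none.

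**6. Which set the cut-off governs.** Section 10 applies the lesson minimum to the group labelled ITT. Section 9 defines the primary analysis population by eligibility and baseline PDFF of at least 10%, with no lesson rule. The Synopsis (Study Design) puts all participants into the secondary and exploratory analyses. These statements do not agree.

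**The case against.** The strongest reply is that the damaging scenario largely cannot occur. The SAP must be final before enrolment ends, and MRIs come 90 to 104 days after each participant starts, so the last participants' outcomes are always unknown at the deadline. With 20 participants at two clinics, accrual could be short enough that no MRI precedes it. This stands, and it makes the MRI part conditional and the size modest.

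The nurse practitioner's monitoring is participant support, and App biometrics are self-reported items, not MRI. Site data sit in a separate system and App data are access-restricted. That also stands. The protocol does not say that the sponsor sees MRI results during accrual. Equally, it sets no firewall and no date before which data may not be reviewed.

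Section 10 does use the word pre-specified. A reader might infer that this settles the matter. It does not, because the only date given for the SAP is the one in Section 11. A reader might equally infer that pre-specification is false here, or that the p-value has lost its error rate. The documents do not support that either: they permit a late choice but do not plan one.

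Finally, if Section 9 governs the primary analysis, the lesson cut-off may not touch it at all, and calling a Per Protocol set ITT is arguably the deeper problem. That is a fair point, and it is why the sections need reconciling. Correcting the SAP date alone would leave a completer-based set in place.

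**Conclusion.** The point holds as a timing rule that the protocol fixes badly. Pre-specification of the lesson cut-off is not guaranteed. The App-data part rests on the protocol's wording and holds at any accrual length. The MRI part holds only if accrual exceeds about 90 to 104 days.

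Under the stated assumptions, the false-benefit rate could rise from 2.5% to about 3 to 4% with half the outcomes seen, and essentially not at all with 2 of 10 seen. About 5% is a ceiling that the deadline rules out and should not be quoted as the expected size. That the study is open-label is inferred from the single arm and the absence of any described blinding. Whether the cut-off governs the primary analysis is itself unresolved in the protocol. The change is worth making because the bias would run towards benefit and the repair is cheap, even in a feasibility study.

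**What to change.** Amend Section 11 so that the SAP, including the lesson minimum, is finalised and dated before the first participant completes App onboarding, or at the latest before any post-baseline App or MRI data are reviewed. The number may stay in the dated SAP and need not move into the protocol.

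Reconcile Section 10 with Section 9 and the Synopsis (Study Design): state whether the lesson minimum applies to the primary analysis, and do not give one set both the Per Protocol and ITT labels. A straightforward solution is to make all enrolled participants with baseline PDFF of at least 10% the primary set and use the lesson-based set as supportive.

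The date change alters no sample size or assessment and costs only earlier drafting of the SAP.

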### 11.1 Primary and Secondary Endpoint Analyses

The primary efficacy endpoint is the change in percent liver fat as measured by MRI-PDFF from baseline to 3 months after enrollment. The results at baseline, at 3 months post-enrollment, and the change from baseline will be summarized descriptively. Change from baseline results will be calculated as (post-baseline minus baseline). The baseline result is defined as the last assessment prior to starting the Better Therapeutics App. In addition, the change from baseline in the percentage liver fat will be tested using a one-sample t-test if the normality assumption is met. The normality assumption will be assessed using the Shapiro-Wilks test for normality. If the normality assumption is not met, then the change from baseline will be tested using a Wilcoxon rank sum test.

The continuous secondary endpoints will be summarized in the same manner as described for the primary efficacy endpoint.

The categorical secondary endpoints, such as the percentage of participants who achieve  $\geq 30\%$  reduction in MRI-PDFF from baseline to post-intervention, will be summarized using counts and percentages. In addition, exact binomial confidence intervals for the true rates will be provided.

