|  | 
Using these results, it was determined a sample size of approximately 8 participants would provide approximately 90% power, assuming an alpha of 0.05. To account for up to a 20% attrition rate, a minimum of 10 participants are required.
 
To ensure inclusion of a mix of patients with either NAFLD or NASH, a total of approximately 20 participants will be enrolled. It's expected that up to 50% of fully eligible participants will fail to meet the MRI-PDFF requirements for inclusion in the primary endpoint analysis, resulting in approximately 10 participants included in the primary endpoint analysis. Participants who do not meet the MRI-PDFF requirement for primary analysis endpoint will be included in secondary and exploratory analyses.
 
Demographics and baseline characteristics will be summarized descriptively for all subjects based on the analysis population. Descriptive summaries will include the number of non-missing observations, mean, median, standard deviation, minimum and maximum for continuous results. Categorical results will be summarized with counts and percentages.
 
Efficacy Analyses
 
The primary efficacy endpoint is the change in percentage liver fat as measured by MRI-PDFF from baseline to 3 months after enrollment in those with a baseline PDFF <math>\geq 10\%</math>. The results at baseline, at 3 months post-enrollment, and the change from baseline will be summarized descriptively. In addition, the change from baseline in the percentage liver fat will be tested using a one-sample t-test if the normality assumption is met. If the normality assumption is not met, then the change from baseline will be tested using a Wilcoxon rank sum test.
 
The continuous secondary and exploratory endpoints will be summarized in the same manner as described for the primary efficacy endpoint.
 
The categorical secondary and exploratory endpoints, such as the percentage of participants who achieve <math>\geq 30\%</math> reduction in PDFF from baseline to post-intervention, will be summarized using counts
 |

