### 3. Outcomes

#### 3.1 Measures of Primary Outcomes

- Mean change in percent liver fat from baseline to end of treatment in participants with baseline PDFF  $\geq 10\%$ , as measured by MRI-PDFF

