## **9. Sample Size**

The primary study population consists of approximately 20 male and female adult participants (18 – 75 years old), with a diagnosis of nonalcoholic fatty liver disease (NAFLD) or nonalcoholic steatohepatitis (NASH), and who satisfy the inclusion and exclusion criteria. Only those who meet PDFF  $\geq 10\%$  will be included in the primary endpoint analysis.

Sample size calculations are estimated for the primary analysis population, i.e. those who satisfy all inclusion/exclusion criteria and have a baseline PDFF  $\geq 10\%$ .

The sample size was calculated by referencing the mean absolute change in steatosis and standard deviation reported in a 2019 JAMA review of the impact to behavioral weight loss interventions on clinical markers of NAFLD (Koutoukidis et al., 2019). The average mean absolute change in steatosis was -2.4 and mean standard deviation was 1.6. Using these results, it was determined a sample size of approximately 8 participants would provide approximately 90% power, assuming an alpha of 0.05. To account for up to a 20% attrition rate, a minimum of 10 participants are required.

To ensure inclusion of a mix of patients with either NAFLD or NASH, a total of approximately 20 participants will be enrolled. It's expected that up to 50% of fully eligible participants will fail to meet the MRI-PDFF requirements for inclusion in the primary analysis population, resulting in approximately 10 participants included in the primary endpoint analysis. Participants who do not meet the MRI-PDFF requirement for primary analysis endpoint will be included in secondary and exploratory analyses.

Demographics and baseline characteristics will be summarized descriptively for all subjects based on the analysis population. Descriptive summaries will include the number of non-missing observations, mean, median, standard deviation, minimum and maximum for continuous results. Categorical results will be summarized with counts and percentages.

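### A Shapiro-Wilk gate on about 8 to 10 changes chooses the primary test; it adds almost no protection and falls back on a two-sample rank test that does not fit the data

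*Protocol*

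**What the plan says.** Section 11.1 of the protocol sets a two-step rule for the change in MRI-PDFF. The first step is the pre-test: "The normality assumption will be assessed using the Shapiro-Wilks test for normality". On a pass, the change "will be tested using a one-sample t-test if the normality assumption is met". On a fail: "If the normality assumption is not met, then the change from baseline will be tested using a Wilcoxon rank sum test". The Statistics part of the synopsis gives the same rule ("tested using a one-sample t-test if the normality assumption is met", otherwise rank sum) without naming the normality test. No level for the pre-test is stated.

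The endpoint in section 3.1 is a mean: "Mean change in percent liver fat from baseline to end of treatment in participants with baseline PDFF" at or above 10%. Section 9 sizes the trial on a mean and an SD: "The average mean absolute change in steatosis was -2.4 and mean standard deviation was 1.6". From these, "it was determined a sample size of approximately 8 participants would provide approximately 90% power", "assuming an alpha of 0.05". Allowing for 20% attrition gives 10. Section 9 expects about 10 of about 20 enrolled participants to enter the primary analysis.

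**The concern.** The test that produces the primary p-value is known only after the changes have been seen. The instrument that picks it is a normality test on 8 to 10 values, where such tests have little power. A report that normality was met would reassure readers more than a sample of this size can justify.

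Two further problems follow from the fallback branch. A rank test does not test a mean, so the gate lets the data change the quantity being tested, away from the stated endpoint and the sample-size basis. And the rank sum test compares two independent groups. A single set of within-person changes has no second group, so the branch cannot be run on those changes as written. Someone following the text literally might compare baseline values with 3-month values as if they came from different people, which discards the pairing.

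**Working it through.** **Inputs from the protocol.** Mean change -2.4 and SD 1.6, so the standardised effect is 2.4/1.6 = 1.5; alpha 0.05; 8 evaluable participants, 10 before attrition (section 9).

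**Assumptions.** Two-sided testing; pre-test level 0.05; skewness of the changes 0, 1, 1.41 or 2 (normal, gamma and exponential shapes), plus a lognormal with sigma 0.7.

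**The plan's own figure.** The power of a two-sided one-sample t-test comes from the noncentral t with n-1 degrees of freedom and noncentrality 1.5 × √n. It is 90.8% at n=7, 95.1% at n=8 and 98.7% at n=10. The stated 8 for about 90% is reproduced on the conservative side, and 8/(1-0.2) = 10 matches.

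**Error of the rule.** Simulated with 40,000 samples per case and a true mean change of 0. The fallback here is the exact signed-rank test, because rank sum has no one-sample form.

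| n | Skewness | Pre-test detects | t-test alone | Two-step rule | Signed-rank alone |
|---|---|---|---|---|---|
| 8 | 0 | about 5% | 4.9% | 5.0% | 3.8% |
| 8 | 1 | 11% | 6.5% | 6.5% | 4.9% |
| 8 | 1.41 | 18% | 8.0% | 7.8% | 6.2% |
| 8 | 2 | 34% | 10.3% | 9.8% | 8.3% |
| 10 | 0 | about 5% | 5.0% | 5.0% | 5.0% |
| 10 | 1 | 14% | 6.4% | 6.4% | 6.0% |
| 10 | 1.41 | 24% | 7.4% | 7.3% | 6.9% |
| 10 | 2 | 45% | 10.0% | 9.4% | 9.1% |

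The largest gain from the gate is 10.0 - 9.4 = 0.6 points. The lognormal (8,000 samples) gives 31% and 40% detection at n=8 and n=10, with two-step error of 10.8% and 9.8% against 11.0% and 10.4% for the t-test. Among samples that pass the gate, with skewness 1 to 2, the t-test's error is 6.8% to 12.4% at n=8 and 6.9% to 12.9% at n=10. A pass is therefore no evidence that the t-test is safe.

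**A larger primary set.** Section 9 says up to 50% will miss the threshold, so the primary set could reach 20, or 20 × 0.8 = 16 after attrition. At skewness 2 the gate then detects 72% (n=16) or 84% (n=20), but the rule's error is 11% and 13%, against 9% and 8% for the t-test alone.

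**The fallback as named.** Suppose rank sum is run on baseline against 3-month values as independent groups, with follow-up equal to baseline plus the planned change. The protocol gives no baseline SD. For a normal baseline with an assumed SD, exact two-sided power is:

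| Assumed baseline SD (points) | n=8 | n=10 |
|---|---|---|
| 3 | 20% | 24% |
| 4 | 7.5% | 7.9% |
| 5 | 2.8% | 2.8% |
| 6 | 1.4% | 1.0% |

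The baseline shape matters too. An SD of 4 with values bunched just above 10% (gamma shape) gives 14% and 17%.

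**Power of the whole rule with that fallback, baseline SD 4.**
- Normal changes, n=8: 0.95 × 0.951 + 0.05 × 0.075 = 0.907, about 91% instead of 95%.
- Normal changes, n=10: 0.95 × 0.987 + 0.05 × 0.079 = 0.942, about 94% instead of 99%.
- Strongly skewed changes (exponential or the lognormal, either direction): simulation with a baseline SD of 3 to 4 gives about 56% to 76%, against 86% to over 99% for the t-test alone.

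**The case against.** The case for leaving the rule alone is substantial.

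- **The rule is pre-specified.** A reader might infer that the analyst is free to choose. The text does not support that: pre-test and both branches are fixed, and the missing pre-test level may be in the statistical analysis plan. A level of 0.10 would raise detection at skewness 2 to 46% (n=8) and 56% (n=10).
- **The gate does not inflate error at 8 to 10.** A reader might infer that it does from the error among passing samples. The relevant figure is the unconditional rate, which tracks the t-test and holds 5% under normality.
- **The recommended t-test is no better on error.** At n=8 to 10 its error equals or slightly exceeds the rule's. This stands.
- **The direction of any excess is unknown.** With a long tail of large reductions, false claims of benefit run at about 0.4% against a nominal 2.5%. Excess error favours the device only under the opposite skew.
- **Little turns on it.** This is a single-arm feasibility study that puts description first. At the planned effect the t-test and signed-rank test disagree in about 0% to 6% of samples.
- **Rank sum may be a slip for signed-rank.** That is plausible, and then the power loss would not arise. The wording would still need correcting.

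These points remove any claim that the error rate is damaged. They do not show that the gate achieves anything, and they do not make the named fallback fit the data.

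**Conclusion.** The point holds as a minor one. At 8 to 10 participants the gate misses most samples with skewness 1 to 2 and changes the error rate by at most about 0.6 points. In return, the primary analysis can switch from the stated mean change to a rank test, and the one named is wrong for a single set of within-person changes. If that test were run on independent groups, power in that branch would be very low. The whole rule would lose about 4 to 5 points with normal changes and considerably more with strongly skewed ones.

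The error figures rest on assumed skewness, and the power figures also on an assumed baseline SD and shape; the protocol gives none of these. The statement that the gate misses most skewness is limited to this size and a 0.05 pre-test. It fails for a more extreme lognormal (sigma 1) at n=10 (60% detected) and for skewness 2 at n=16 to 20. At those larger sizes the rule has higher error than the t-test under that skew, so the gate still does not help.

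**What to change.** In section 11.1 and in the Statistics part of the synopsis:

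1. Delete the normality gate.
2. Name the one-sample t-test on the change, with its 95% CI, as the single primary test. This matches the mean-change endpoint and the sample-size calculation.
3. State that the exact Wilcoxon signed-rank test (not rank sum) on the within-person changes will always be reported as a fixed sensitivity analysis.

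Sections 11.1 and 11.2 carry the primary methods over to the continuous secondary and the exploratory endpoints, so the same wording should apply there.

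The cost is about one sentence in each place, with no new data. There is one small statistical cost: under strong skew at 8 to 10 participants, the t-test's error is up to about 0.6 points above the two-step rule's. The signed-rank result shown alongside lets the reader see any disagreement.
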